## Materials and methods

### Research design

This study is a randomized, assessor-blind, three-arm, superiority, parallel controlled trial. Participants will be randomly assigned to the HIIT group, MICT group, or guideline group. Testing will be performed at baseline and after the 12-week intervention. The minimum attendance rate will be established in light of the least beneficial dose of exercise. According to previous research (Abreu et al., 2021), participants who complete fewer than 24 training sessions will be considered to drop out of the study. All health and fitness tests will be conducted using the same equipment at the different testing sites. All blood samples will be measured by the same type of facility, and all blood samples will be stored in the Experimental Center of China Medical University for subsequent analysis. An overview of the trial procedures is displayed in Figure 1. This study was approved by the Ethics Review Committee of the Reproductive Hospital Affiliated to China Medical University (approval no. 202203, China clinical trial registration number: ChiCTR2200061573^1^). All patients will provide written informed consent prior to enrollment, and the results of the study will be reported following the Consolidated Standards of Reporting Trials (CONSORT) guidelines.

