### Research setting

We will recruit 330 eligible T2DM participants from 3 communities in Shenyang by posters, leaflets and brochures and by conducting health seminars; community physicians will be involved in participant recruitment. All diagnostic participants will be evaluated by clinicians. The exercise interventions and measurements of anthropometric parameters and physiological indicators will be performed at community exercise clinics. The research staff who blinded to group allocation will collect baseline data, supervise the training, and finish outcomes related test in clinical exercise physiology. Participants was initial enrolled in June 2022 and the recruitment is still undergoing.

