### Random assignment and blinding

After the baseline assessment, we will randomly assign the participants into three equal groups (1:1:1), namely, the HIIT group, MICT group, and guideline group. This study is an assessor-blind randomized controlled trial, and indicators will be measured at baseline and after 12 weeks by assessors blinded to group allocation. Study interventions will be delivered by study staff. A randomization table will be provided by the Department of Statistics, School of Public Health, Fudan University (Excel software; Microsoft). Study staff who blinded to the group allocation will collect the measurements and maintain possession of the randomization table. The group allocation of participants will be recorded on a paper in an opaque envelope that will only be opened after the baseline assessment of participants has been completed.

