#### HIIT group

Participants will perform training with supervision, involving walking on a flat or inclined treadmill 3 times a week. The HIIT protocol consists of a 10-min warm-up (at 50–60% of the peak HR), 10 × 1-min intervals at 85–95% of the peak HR separated by 1-min periods of active recovery (at 60–70% of the peak HR), and a final 5-min cooldown, which corresponds to the Borg RPE scale of 16–17. An HR monitor (Polar Electro, Kempele, Finland) will be used to obtain the training HR. The speed and incline of the treadmill will be continuously adjusted to ensure that each training session is performed at the prescribed HR.

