#### MICT group

Similar to the HIIT group, the participants in the MICT group will perform training with supervision, involving walking on a flat or inclined treadmill 3 times a week. Corresponding to the amount of exercise (exercise intensity × duration) of the HIIT sessions, each MICT session will consist of a 5-min warm-up period and a 5-min cooldown period at 30% of the peak HR, separated by 35 min of exercise at 65–75% of the peak HR. An HR monitor (Polar Electro, Kempele, Finland) will be used to obtain the training HR. The speed and incline of the treadmill will be continuously adjusted to ensure that each training session is performed at the prescribed HR.

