### Measurements

The research assistants who blinded to group allocation will collect baseline data from the patients, including age, course of the disease, height, weight, blood pressure, smoking history, socioeconomic status, time since retirement, and history of antidiabetic medication. These assessments will provide a comprehensive overview of the participants’ characteristics. The primary outcome measures of the study will be the HbA1c and BDNF levels. Additionally, the secondary outcome measures will include physical activity levels, anthropometric parameters (weight, waist circumference, hip circumference, and BMI), physical parameters (including fat percentage, muscle percentage, and the fitness rate), cardiorespiratory fitness indicators (blood pressure, the heart rate, vital capacity, and maximum oxygen consumption), biochemical indicators (high-density lipoprotein, low-density lipoprotein, triglyceride, total cholesterol, and HbA1c), inflammation level (C-reactive protein), cognitive function (assessed through reaction time and dual-task gait test performance), and motor function (evaluated through static balance, dynamic balance, single-task gait test performance, and grip strength). To collect these data, participants will be assessed before the start of the intervention and again after the 12-week intervention. Notably, all exercise tests and data collection will be conducted by research assistants blinded to patient group allocation.

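### Staff described as blinded are assigned both to supervise training and to run the outcome tests, which contradicts the assessor-blind design for the performance-based secondary outcomes

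*Protocol article*

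**What the plan says.** All references are to the protocol article.

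- **Research design** makes blinding part of the design: "This study is a randomized, assessor-blind, three-arm, superiority, parallel controlled trial".
- **Research setting** gives three tasks to one group: "The research staff who blinded to group allocation will collect baseline data, supervise the training, and finish outcomes related test in clinical exercise physiology".
- **Random assignment and blinding** says that "indicators will be measured at baseline and after 12 weeks by assessors blinded to group allocation". It adds "Study interventions will be delivered by study staff", without saying whether these staff are separate from the assessors. It also says: "Study staff who blinded to the group allocation will collect the measurements and maintain possession of the randomization table".
- **Measurements** repeats the claim: "all exercise tests and data collection will be conducted by research assistants blinded to patient group allocation".
- **HIIT group** describes "10 × 1-min intervals at 85–95% of the peak HR separated by 1-min periods of active recovery". **MICT group** describes a warm-up and a cooldown "separated by 35 min of exercise at 65–75% of the peak HR". Both are supervised three times a week, with treadmill speed and incline adjusted throughout to hold the prescribed heart rate.
- **Guideline group** describes one supervised session followed by weekly remote monitoring by smartphone.

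**The concern.** Supervising training and being blind to the arm are incompatible in this trial. If the Research setting sentence is followed as written, the person who runs a participant's week-12 tests may have trained that participant for 12 weeks.

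Several secondary outcomes can be moved by how hard the tester encourages the participant or by when the tester starts and stops the clock. The Abstract states a hypothesis that favours both supervised arms over the guideline arm, and HIIT most of all. Assessor blinding is meant to stop such an expectation from reaching the data, and none of the planned analyses (mixed model, multiple imputation, per-protocol sensitivity analysis) can remove the bias afterwards.

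**Working it through.** The protocol gives no figure on this point, so the check is mainly a comparison of statements.

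**1. Can a training supervisor be blind?** No. HIIT consists of ten one-minute bouts at 85–95% of peak heart rate with active recovery. MICT is 35 minutes at 65–75%. The two look different, and the supervisor must know the target in order to adjust the treadmill to it. Training intervention also requires intensity, duration and heart rate to be recorded.

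**2. Does any section separate trainers from testers?** No. Random assignment and blinding names assessors in one sentence and study staff in another, but does not say that they are different people. Measurements calls the testers blinded and does not say who trains.

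**3. Is there a second route to the allocation?** Yes. The staff who take the measurements are said to hold the randomization table. The opaque envelopes, opened only after baseline, do not help if the tester has the table.

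**4. When does it matter?** Randomization follows the baseline assessment, so knowledge gained by supervising training affects the week-12 tests. Access to the table could matter at both visits.

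**5. Which outcomes are exposed?** The secondary items listed under Measurements are: physical activity 1, anthropometry 4, physical parameters 3, cardiorespiratory 4, biochemistry 5, C-reactive protein 1, cognitive 2, motor 4. The total is 1 + 4 + 3 + 4 + 5 + 1 + 2 + 4 = 24.

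- Performance tests (8): vital capacity, maximum oxygen consumption (exercise test to volitional exhaustion), reaction time, dual-task gait, one-leg stand, Y balance, single-task gait, grip strength. Gait is less exposed, because it is walked at normal pace and recorded by a pressure-plate system.
- Adding the items that depend on the tester's reading (waist, hip, blood pressure): 8 + 3 = 11.
- The exposed share is therefore 8 to 11 of 24.

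**6. How large could the effect be?** The documents give no figure for differential encouragement, so a range is assumed. Evaluable participants per arm, from Sample size calculation: 110 × (1 − 0.20) = 88. For a shift of d standard deviations with no true effect, the noncentrality is d × √(88/2), and the two-sided 5% rejection rate is Φ(nc − 1.96) + Φ(−nc − 1.96).

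| Assumed d (SD) | Noncentrality | False-positive rate |
|---|---|---|
| 0 | 0 | 5% |
| 0.1 | 0.1 × 6.633 = 0.663 | about 10% |
| 0.2 | 0.2 × 6.633 = 1.327 | about 26% |
| 0.3 | 0.3 × 6.633 = 1.990 | about 51% |

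**The case against.** The strongest reply is that the Research setting sentence is loosely written and describes a team, not individuals. Some members may train and others test, with the word for blinded simply misplaced. The use of different nouns elsewhere (assessors, study staff, research assistants) fits that reading. This stands in part: a reader might infer that the protocol proves the same people train and test each participant, and it does not. But no section states the split, and even on the team reading the sentence still calls training supervisors blinded, which cannot be true.

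Three other stronger readings are tempting and not supported:

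- *That absence from training gives the guideline arm away.* Guideline participants have one supervised session, and with three communities a tester may simply not have met a given HIIT or MICT participant.
- *That most secondary outcomes are affected.* The count gives 8 to 11 of 24.
- *That HIIT against MICT is biased in the same way.* Both arms are supervised, so encouragement of one's own trainees does not obviously favour either. The exposure lies mainly in comparisons with the guideline arm.

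It is also fair to say that the superiority rule uses only HbA1c and BDNF, and that Statistical analysis calls the secondary outcomes exploratory. That lowers the severity but does not make the blinding statement correct.

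**Conclusion.** The point holds as a contradiction in the protocol. The Research setting sentence cannot be reconciled with the assessor-blind statements under Research design, Random assignment and blinding, and Measurements, and custody of the randomization table adds to the problem.

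The consequence is limited to the performance-based or tester-dependent secondary outcomes. A reader might infer that the primary results are compromised. The documents do not support that: HbA1c is measured by an automated analyser and BDNF by ELISA, so both are largely protected.

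The 10%, 26% and 51% figures rest wholly on assumed shifts of 0.1, 0.2 and 0.3 SD and on 88 evaluable participants per arm. They show sensitivity and do not estimate the bias in this trial. The recommendation does not depend on them.

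Severity: should be fixed. No confirmatory conclusion rests on the exposed outcomes, but they carry the trial's claims on fitness, motor function and directly tested cognition.

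**What to change.** 1. Reconcile Research setting, Random assignment and blinding, and Measurements so that they say one thing: training is supervised by intervention staff, and baseline and week-12 tests are done by staff with no training role for that participant.
2. State that testers have no access to the randomization table, and name by role who holds it.
3. Ask participants not to disclose their group to the tester.
4. Recruitment began in June 2022 and is described as ongoing, so new wording cannot restore blinding for tests already done. For any participant already tested by his or her own trainer, record this, and do not report the affected outcomes as assessor-blind.

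Cost: a text change and a revised roster. Staff who train in one of the three communities could test in another, at the price of some travel. Whether existing staff suffice cannot be judged, because the protocol gives no staffing numbers. Sample size, endpoints and interventions are unchanged.

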### Inclusion criteria

Participants will be included for both of the following criteria: (1) self-reported physical activity of < 150 min per week of moderate-intensity for the past 6 months, (2) accelerometer measured energy consumption of ≤ 1.5 metabolic equivalents (METs) according to previous study of Ku et al. (2017). Briefly, participants will wear the accelerometers continuously for 7 days (5 weekdays and 2 weekend days, excepting bedtime). The average energy consumption will be calculated with a requirement of for a minimum of 10 h per day of 7 days. (3) Have T2DM and regularly take oral hypoglycemic drugs, (4) age ≥ 65 years, (5) consciousness and ability to volunteer for exercise intervention, (6) lack a self-reported hypertension diagnosed by physician or hypertension with well-controlled blood pressure (< 140/90 mmHg).

### Exclusion criteria

Patients who meet any of the following criteria will be excluded: patients with (1) inability to exercise or other diseases that may affect their physical activity; (2) cognitive disorder; (3) serious comorbidities or complications, such as heart failure, autonomic neuropathy, and recent stroke; (4) a high risk of falling; (5) a history of cancer; or (6) end-stage renal disease dialysis.

### Random assignment and blinding

After the baseline assessment, we will randomly assign the participants into three equal groups (1:1:1), namely, the HIIT group, MICT group, and guideline group. This study is an assessor-blind randomized controlled trial, and indicators will be measured at baseline and after 12 weeks by assessors blinded to group allocation. Study interventions will be delivered by study staff. A randomization table will be provided by the Department of Statistics, School of Public Health, Fudan University (Excel software; Microsoft). Study staff who blinded to the group allocation will collect the measurements and maintain possession of the randomization table. The group allocation of participants will be recorded on a paper in an opaque envelope that will only be opened after the baseline assessment of participants has been completed.

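### As written, neither allocation concealment nor assessor blinding is secured: the measuring staff hold the randomization table, and the blinded staff also supervise the training

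*Protocol article*

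**What the plan says.** The protocol article claims assessor blinding in several places. Research design: "This study is a randomized, assessor-blind, three-arm, superiority, parallel controlled trial". Random assignment and blinding: "indicators will be measured at baseline and after 12 weeks by assessors blinded to group allocation". Measurements: "all exercise tests and data collection will be conducted by research assistants blinded to patient group allocation".

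For concealment, Random assignment and blinding says that each allocation is "recorded on a paper in an opaque envelope that will only be opened after the baseline assessment of participants has been completed". On the origin of the list it says: "A randomization table will be provided by the Department of Statistics", naming a department at another university.

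Two sentences assign duties that do not fit those claims:

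- Random assignment and blinding, on custody: "Study staff who blinded to the group allocation will collect the measurements and maintain possession of the randomization table".
- Research setting, on staff roles: "The research staff who blinded to group allocation will collect baseline data, supervise the training, and finish outcomes related test in clinical exercise physiology".

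**The concern.** Concealment requires that nobody involved in entering or assessing a participant can learn the next allocation before that participant is committed. Assessor blinding requires that nobody who measures a participant can learn the arm before the last measurement. The article gives the list to the people who measure at both time points, and gives blinded people a task that reveals the arm.

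The two protections guard against different biases. If concealment is lost, knowledge of the coming arm can influence who enters or how the baseline is recorded. That changes the composition of the arms and can reach every outcome, both primaries included. If assessor blinding is lost, the week-12 measurement can be influenced wherever the tester's judgement, timing or encouragement affects the result. Analysis cannot reliably repair either loss.

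**Working it through.** No arithmetic applies. The point depends on no alpha, power, effect size, SD or dropout figure, and the sample size is unaffected. The check is to set the statements side by side.

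**Step 1. Who holds the table?** The custody sentence has one subject and two verbs: the same staff collect the measurements and keep the table. The article nowhere says that the table is coded, sealed, held by a third party or otherwise unreadable to its holders.

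**Step 2. What does this do to concealment?** Consent and screening come first (Intervention), then the baseline assessment, then the opening of the envelope (Random assignment and blinding). The envelope is meant to keep the allocation unknown throughout the baseline assessment. The staff collecting baseline data have the list from which the envelopes are filled, so the envelope does not by itself keep the next allocation from them. Some exclusion criteria, such as inability to exercise, serious comorbidity and high risk of falling, leave room for judgement, so there is something that foreknowledge could influence.

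**Step 3. What does it do to blinding at week 12?** The same staff measure again at the end of the intervention. A readable list lets them look up any participant's arm. The claim that they are blinded then rests on their not looking.

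**Step 4. Does the rest of the article separate the roles?** It does not. Research setting gives blinded staff three duties: baseline data, training supervision and outcome tests. HIIT sessions alternate 1-minute intervals with 1-minute recovery, MICT sessions are 35 minutes of continuous exercise, and the guideline group is followed remotely after one supervised session. Anyone supervising a treadmill session knows which arm it is. This is a second contradiction, independent of custody of the table.

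**Step 5. Which outcomes are exposed, and by which route?**

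| Outcome | Route through lost concealment | Route through lost assessor blinding |
|---|---|---|
| HbA1c (fully automated HPLC analyzer, duplicate readings averaged) | Yes | Little |
| BDNF (ELISA, run to the manufacturer's instructions) | Yes | Little |
| Exercise testing (continued to volitional exhaustion) | Yes | Yes |
| Static balance (timed by the tester) | Yes | Yes |
| Dynamic balance, grip strength, reaction time, gait (depend on effort and instruction) | Yes | Yes |

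The primary outcomes are therefore reached through concealment and scarcely through measurement. The motor-function outcomes, the cognitive performance tests and the exercise test are reached by both routes.

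**The case against.** The strongest reply is that this may be a drafting fault and not a custody fault. The sentence itself calls the table-holders blinded, the claim of blinding recurs elsewhere, and the English is imperfect. Two groups of staff may have been merged into one sentence, or the table may be held coded or sealed. Either would remove the problem. That stands as far as the facts of conduct go: the article does not prove that anyone saw an allocation. It does not rescue the text, because the article states neither arrangement and makes the same kind of merger again in Research setting. Nor is this detail left to a fuller document, because the article positively assigns custody.

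A second reply is that measuring staff are not said to decide eligibility. Community physicians help with recruitment and clinicians evaluate participants. That also stands, so influence on entry is a possibility and not a documented route. Influence on the baseline assessment is closer at hand, since these staff carry it out.

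Third, the analysis includes baseline values, which could absorb some imbalance in baseline HbA1c or BDNF. It cannot be relied on to remove selection on frailty or other prognosis that those values do not capture.

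Fourth, the secondary outcomes are declared exploratory. This lowers the stakes of lost assessor blinding but does not remove them, because the trial's stated hypotheses on motor function, cognitive function and cardiopulmonary function draw on these tests.

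**Conclusion.** The point holds as a contradiction in the stated procedure that must be corrected: as written, neither allocation concealment nor assessor blinding is secured. It rests on reading the two staffing sentences literally and on the absence of any statement that the table is unreadable to its holders.

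A reader might infer three stronger conclusions that the article does not support:

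- That the envelopes are certainly defeated and the assessors cannot be blind. Possession of the list permits this but does not establish it, since a holder may not look and the table may be coded.
- That unblinded measurement undermines the primary outcomes. HbA1c and BDNF are laboratory readings with little scope for assessor influence; only the concealment route reaches them.
- That the false-positive rate rises by some stated amount. The article gives nothing from which to derive the size of a bias, and any figure would restate an assumed shift. No magnitude is claimed.

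**What to change.** Replace the custody sentence in Random assignment and blinding with text to this effect:

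> The randomization table is held only by the Department of Statistics that generates it, or by another named role with no part in enrolment, training or assessment. Allocations are released one at a time, in sealed, sequentially numbered opaque envelopes, to intervention staff after the participant's baseline data have been recorded. Staff who collect measurements have no access to the table or the envelopes.

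In Research setting, remove training supervision from the duties of the blinded staff and assign it to separate intervention staff.

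Enrolment began in June 2022 and was still under way when the article was written, so custody cannot be changed for participants already randomized. For them, document and report who had access to the table and when. If separate staff in fact held it, correct the sentence and say so.

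The cost is a minor change in custody and logistics across three communities. The article does not say whether the Department of Statistics can release allocations one at a time, which is why an independent local holder is offered as the alternative. Sample size and analysis need no change.
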